### Statistical analysis

The statistical analysis plan has been developed to align with the study objectives and ensure rigorous evaluation of outcomes. Descriptive statistics will be used to summarize baseline characteristics across study arms. Continuous primary and secondary outcomes will be assessed for normality prior to analysis. Between-group comparisons of mean changes from baseline to study completion will be conducted using analysis of variance (ANOVA) for normally distributed data or the Kruskal–Wallis test for non-normal data. Within-group pre–post changes will be analyzed using paired-sample *t*-tests or Wilcoxon signed-rank tests, as appropriate.

To account for baseline imbalances and potential confounding factors such as age, sex, and baseline outcome values, analysis of covariance (ANCOVA) will be applied, with adjusted mean differences reported alongside 95% confidence intervals. Categorical variables will be compared between groups using the Chi-square test or Fisher’s exact test, as appropriate.

Missing outcome data will be handled using multiple imputation methods to minimize bias and improve the robustness of estimates. The primary analysis will follow the intention-to-treat principle for all efficacy and safety outcomes, with a secondary per-protocol analysis conducted for efficacy outcomes among participants who complete the follow-up assessments. All statistical analyses will be performed using SPSS software (version 20.0), with a two-sided significance level set at *α* = 0.05.

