### Method of data analysis

For both primary and secondary outcome measures, mean values at baseline and study completion, as well as mean differences, will be compared across the two study arms using ANOVA (Analysis of Variance) or the non-parametric Kruskal–Walli’s test, depending on the data’s normality. Within each treatment arm, changes in primary and secondary outcomes before and after the intervention will be analyzed using either paired-sample *t*-tests or the non-parametric Wilcoxon signed-rank test, based on the distribution of the data. For all normally distributed outcomes, 95% confidence intervals will be calculated. Categorical variables will be analyzed between groups using the Chi-square test. Potential confounding factors will be adjusted using ANCOVA, with adjusted mean values and corresponding confidence intervals subsequently calculated and reported. Regarding missing data, instead of the last observation carried forward, multiple imputation techniques will be employed to handle missing outcome data, ensuring a more robust and unbiased estimation. Statistical analysis will be conducted using the SPSS software (version 20.0), and the level of significance will be set at *α* = 0.05. In cases of missing outcome data, the most recent available values of the outcome measures will be used as replacements. Intention-to-treat analysis will be applied for all efficacy and safety outcomes. Additionally, per-protocol analysis will be conducted for efficacy outcomes, including only participants who complete the follow-up.

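### Several between-arm tests are planned for the same primary question and none is said to decide it; the baseline-adjusted ANCOVA already in the plan should be that test

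*Protocol article*

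**What the plan says.** Two sections of the protocol article describe the efficacy analysis.

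**Method of data analysis.** For primary and secondary outcomes, "mean values at baseline and study completion, as well as mean differences, will be compared across the two study arms using ANOVA", or Kruskal–Wallis, depending on normality. Three quantities are therefore compared between arms: baseline means, final means and differences. The section adds "For all normally distributed outcomes, 95% confidence intervals will be calculated" and then "Potential confounding factors will be adjusted using ANCOVA, with adjusted mean values and corresponding confidence intervals subsequently calculated and reported", with no covariates listed.

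**Statistical analysis.** "Continuous primary and secondary outcomes will be assessed for normality prior to analysis", with no criterion given. The lead comparison is stated as "Between-group comparisons of mean changes from baseline to study completion will be conducted using analysis of variance (ANOVA) for normally distributed data"; where that check fails, Kruskal–Wallis takes its place. An ANCOVA is added: "To account for baseline imbalances and potential confounding factors such as age, sex, and baseline outcome values, analysis of covariance (ANCOVA) will be applied". Its output is to be an adjusted difference between arms and its 95% interval. Baseline characteristics are to be summarised descriptively.

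Both sections also plan within-arm pre–post tests (paired t or Wilcoxon signed-rank). Alpha is 0.05 throughout. The term primary analysis appears only in connection with the intention-to-treat principle, not with any test.

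**The concern.** For one question (does BMFD differ from placebo on a primary outcome?) the article lists final-value ANOVA, change-score ANOVA, a Kruskal–Wallis replacement for either, and ANCOVA. They are not ranked. Three things are at stake.

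- **Selection.** Several p-values for the same contrast, each at 0.05, leave room to report the favourable one.
- **Target of estimation.** A normality check on the trial's own data decides whether the unadjusted result is a difference in means or a comparison of ranks.
- **Precision.** An unadjusted change score subtracts the whole baseline value, whatever the correlation between baseline and follow-up. ANCOVA subtracts only as much as the data support.

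Two smaller points follow from the same text. Testing baseline means between randomised arms asks whether a chance difference is due to chance, and the two sections disagree on whether to do it. Within-arm tests carry no label that separates them from the evidence on efficacy, although they cannot distinguish the product from the passage of time or repeat testing.

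**Working it through.** **Inputs from the article (Sample size; Statistical analysis).** Difference 0.5 kb, SD 0.7 kb, two-sided alpha 0.05, power 80%, dropout 10%, 37 per arm. Evaluable per arm: 37 × 0.9 = 33.3, taken as 33.

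**Inputs not in the article.** The correlation r between baseline and follow-up, and whether 0.7 kb is the SD of one value or of a change. Both are treated as assumptions and shown as ranges.

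**Step 1: the stated sample size.** n per arm = 2 × [0.7 × (1.960 + 0.842) / 0.5]² = 30.8, so 31, and 31/0.9 gives 35. The exact t-test needs 32, which gives 36. The stated 37 is reproduced to within two participants and is not in dispute.

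**Step 2: free choice among the tests.** Null normal data were simulated with 33 per arm (20,000 runs per setting). Each test alone rejects about 5% of the time. Rejection by at least one of final-value comparison, change-score comparison and ANCOVA:

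| r | Any of the three |
|---|---|
| 0.3 | 9.1% |
| 0.5 | 9.5% |
| 0.8 | 10.0% |

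A repeat with 40,000 runs per setting gave 9.3%, 9.7% and 10.2%. If the choice is only between the normality-switched change-score test and ANCOVA, the figure is about 6–8%.

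**Step 3: precision.** With equal variance σ² at both visits:

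- variance of change = 2σ²(1 − r)
- ANCOVA residual variance = σ²(1 − r²)
- ratio, ANCOVA to change = (1 + r)/2

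The ratio is 0.65 at r = 0.3, 0.75 at 0.5 and 0.90 at 0.8.

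**Step 4: power at 33 per arm if 0.7 kb is the SD of a single value (t-based).**

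| r | SD of change | Change-score power | ANCOVA residual SD | ANCOVA power |
|---|---|---|---|---|
| 0.3 | 0.828 | 67.6% | 0.668 | 85.0% |
| 0.5 | 0.700 | 81.5% | 0.606 | 91.0% |
| 0.8 | 0.443 | 99.5% | 0.420 | 99.7% |

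Change-score power reaches 80% at r of about 0.48.

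**Step 5: if 0.7 kb is the SD of change.** Change-score power at 33 per arm is 81.5% whatever r is, so there is no shortfall. ANCOVA would still gain: before dropout it needs 20, 24 and 30 per arm at r = 0.3, 0.5 and 0.9, against 31.

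**Step 6: the normality switch alone.** The two-stage procedure was simulated with Shapiro–Wilk in each arm as an assumed check, 6,000 runs per setting. On normal data its type I error was 4.8–5.4%. On lognormal data it had more power than ANCOVA on the raw scale: 90% against 85% at r = 0.3, and 96% against 88% at r = 0.5.

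**The case against.** The strongest reply is that this is a condensed article. It says an analysis plan has been developed, and the deciding model, the normality criterion and the final covariate list are commonly fixed there. That would answer a complaint that detail is absent. It does not answer this one: the article itself states several tests of the same contrast, and its two sections treat baseline comparisons differently.

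Several stronger readings are tempting, and the document does not support them.

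- *The change-score test is the designated primary test.* No test is so labelled; that is the defect.
- *ANCOVA is left undefined.* It names baseline, age and sex, and its output. Only its rank and the final covariate list are open.
- *Covariates will be picked from observed imbalances.* Accounting for imbalance is given as a purpose; no selection step is described.
- *A non-normal outcome gets no confidence interval.* The sentence limiting intervals to normally distributed outcomes invites this, but both sections promise ANCOVA intervals without that condition.
- *The normality check itself inflates type I error.* Step 6 shows that it does not.
- *ANCOVA can never do worse.* Its advantage over the change score is a large-sample result, which fails negligibly at r of about 0.97 or more with 66 evaluable participants. It does not extend to Kruskal–Wallis on skewed data (Step 6).
- *Selection on MoCA of 24 or above would mimic improvement through regression to the mean.* A lower cut-off makes later scores drift down, and MoCA is not a primary outcome.

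**Conclusion.** The point holds as a fault of unranked, competing analyses. Its size is a type I error of about 9–10% in place of 5%, assuming normal data, 33 evaluable per arm, and that any of the final-value, change-score or ANCOVA results could be claimed. The document does not say that such selection will occur; it leaves it open.

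The loss of precision from the unadjusted change score is real, but its size is unknown. Power falls below 80% only if 0.7 kb is a single-value SD and r is under about 0.48. At high r the gain from ANCOVA is negligible, and if 0.7 kb is the SD of change there is no shortfall. A reader should not conclude that the trial is underpowered.

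The change should be made: it replaces a stated set of methods with one that is clearer and usually more precise.

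**What to change.** In both analysis sections:

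1. Name the ANCOVA already planned as the single deciding between-arm analysis for each primary outcome: follow-up value on arm, baseline value of the same outcome, age and sex. Close the covariate list, and report the adjusted difference with its 95% confidence interval.
2. Pre-specify a log scale for any primary outcome expected to be skewed, since raw-scale ANCOVA can lose to a rank test there.
3. Keep the unadjusted change-score and rank-based tests as sensitivity analyses, run regardless of any normality check.
4. Delete the between-arm tests of baseline means from Method of data analysis, in line with the descriptive summary in Statistical analysis.
5. Label within-arm pre–post changes as descriptive.

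The cost is wording only. Age, sex and baseline outcome values are already named as covariates, so no new data and no change to the sample size are needed. The change should be made before allocation is unblinded.

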## Discussion

As per modern science, aging is the time-dependent, physiological decline of biological processes that are often associated with age-related diseases. Those pathologies often associated with aging, such as cellular inflammation and atherosclerosis, involve hyperactivity or uncontrolled cellular growth. There are about nine hallmarks of aging: genomic instability, telomere attrition, epigenetic alteration, loss of proteostasis, deregulated nutrient sensing, mitochondrial dysfunction, cellular senescence, stem cell exhaustion, and altered intracellular communication (49). The hallmark of anti-aging action is calorie restriction (CR), which involves the extension of the life span and the suppression of age-related diseases. Calorie restriction mechanisms play a major role in modulating chronic inflammation at the molecular level, the impact of epigenetic chromatin and histone modification, and the ultimate control of gene expression (50). Changes in telomere length and telomerase activity could provide valuable insights into the potential influence of *Bacopa monnieri* on aging-related processes. Since telomere shortening is a hallmark of cellular aging and genomic instability, any modulation in its length may indicate an impact on biological aging. Similarly, alterations in telomerase activity could reflect the extent to which *Bacopa monnieri* influences cellular longevity and regenerative capacity. Investigating these changes will help determine whether *Bacopa monnieri* plays a role in slowing down aging-related cellular decline or enhancing genome stability.

Gene sequences called telomeres are found at the ends of chromosomes and are in charge of preserving the integrity of the genome. Telomere length is at its maximum at birth and decreases progressively with advancing age; thus, it is considered a biomarker of chronological aging. Telomerase is the enzyme responsible for maintaining the length of telomeres by adding guanine-rich repetitive sequences. Telomerase activity is exhibited in gametes, stem cells, and tumor cells. Our research team has designed a two-arm, open-label, non-inferiority randomized controlled trial to evaluate the effects of a freeze-dried *Bacopa monnieri* formulation on aging, neurocognitive functions, and constitution (*Prakriti*) in healthy adults, compared to a placebo and his clinical trial will provide evidence-based scientific data on the effectiveness of *Bacopa* and its Ayurvedic dosage form, BMFD, in the aging process and cognitive enhancement concerning individual constitution (*Prakriti*). This trial is expected to contribute to the early diagnosis of neurocognitive impairment and aging-related neurophysiological changes in relation to individual constitution (*Prakriti*). Editorial reflections in aging science emphasize that frailty and cognitive decline represent complex, multidimensional challenges that require integrative biological and socio-cultural strategies (51). By combining traditional Ayurvedic constitutional assessment with modern biomarkers of cellular aging and neurophysiology, this trial contributes to a broader interdisciplinary effort to develop culturally grounded, personalized geriatric interventions.

## Strengths and limitations

This randomized controlled clinical trial evaluates the effects of a freeze-dried formulation of the *Bacopa monnieri* herbal supplement on aging and cognitive function in relation to constitution (*Prakriti*) in healthy adults and multiple outcome measures, including neurocognitive function, telomerase activity, telomere length, nerve conduction tests (NCT), and electroencephalography (EEG), provide a comprehensive assessment of the intervention’s effects. Participants with the MoCA score of 24 or above will be recruited. The findings of this study will offer valuable evidence supporting the use of this herbal preparation in managing age-related neurocognitive decline and neurodegenerative conditions. The study is conducted within a specific population, which may limit the generalizability of the findings.
